## Abstract

**Background:**

Experts in Traditional Chinese Medicine (TCM) have studied the TCM subject of the pathogenesis of heart failure (HF) for several decades. As a result, the general idea is *ben *deficiency and *biao *excess. However, the clinical evaluation system which combined the TCM and western medicine in HF has not been developed yet. The objective is to establish the evaluation index system for the integration of TCM and western medicine. The evaluation indexes which include TCM items will specify the research design and methods.

**Methods:**

Nine medical centers in different cities in China will participate in the trial. A population of 340 patients with HF will be enrolled through a central randomized system for different test groups. Group A will be treated with only western medicine, while group B with western and Chinese medicine together. The study will last for 12 months from the date of enrollment. The cardiovascular death will be the primary outcome.

**Discussion:**

By putting the protocol into practice, the clinical effects of TCM for HF will be identified scientifically, objectively as well as rationally. The proper index system which built in the study will be helpful for the clinical effect expression of HF by integrated medicine in future.

**Trial Registration:**

ChiCTR-TRC-00000059

## Background

Ancient TCM literatures have records of successful treatment methods for heart failure. In modern times, medical experts have recognized the general idea of heart failure in TCM pathogenesis as *ben *deficiency and *biao *excess [1,2]. They have revealed the multi-mechanisms of its efficiency of HF as well [3]. Nowadays, lots of intravenous and oral preparations have been applied in treating HF, and confirmed that they're effective [4-7]. However, the formations of projects involving randomized clinical trials in TCM are recent and their designs are not as rigorous as the clinical trials in western medicine. In this way, neither the conclusion which defined by death nor the special clinical effects of TCM in HF was revealed properly. This restricted the application and development of TCM in HF deadly.

### Objective

In order to evaluate the clinical effects of heart failure and establish a clinical effect expression of HF treated with integrated medicine, the protocol of SECETCM-HF will be implemented. It was strictly designed under the law of randomized controlled trial (RCT).

## Methods

### Design

The multi-centre randomized controlled trial will be practiced in 9 hospitals in Tianjin, Beijing and Shanxi Province of China. The trial begins on September 17^th ^2008.

### Ethical Aspects

The trial was approved by the Ethics Committee of First Teaching Hospital of Tianjin University of TCM on January the 30^th^, 2008 (TYLL2008004). It's registered in the Chinese Clinical Trial Registry and the International Clinical Trials Registry Platform of WHO as well. The protocol and its informed consent form had been judged by the Committee to be ethically and scientifically satisfactory to the aims. Written informed consent must be obtained from all participants or their representatives before enrolling.

### Patients

According to the inclusion and exclusion criteria, totally 340 cases with HF will be randomized into two groups, that are Group A (regular medication group, as comparison) and Group B (regular medication + TCM syndrome differentiation group).

Inclusion criteria are:

• Chronic heart failure patients (The medical history of primary cardiovascular diseases; symptoms and signs typical of heart failure; LVEF≤50%).

• Cardiac function classification: New York Heart Association (NYHA) II ~IV.

• Aged 40-79.

• Completed and submitted informed consent form.

Exclusion criteria are:

• Those whose Brain Natriuretic Peptide (BNP) < 200 pg/mL

• Those who suffer from acute heart failure.

• Those who have one of the following disease: 1) acute myocardial infarction(within the previous 4 weeks); 2) pulmonary heart disease; 3) severe valve disease; 4) hypertrophic obstructive cardiomyopathy; 5) congenital heart disease; 6) pulmonary hypertension which was caused by acute or chronic pulmonary embolism or other reasons; 7) pre-excitation syndrome; 8) stroke within 6 months; 9) acute myocarditis.

• Those who suffer from sever hepatic or renal deficiency.

• Those who have severe endocrine diseases like hyperthyroidism.

• Those who suffer from severe anemia.

• Those who have mental disease.

• Those women who are pregnant or during the lactation period.

• Those who participated in other studies within the last two months.

### Western medication

According to the guidelines for chronic heart failure [8,9], the diuretics, angiotensin converting enzyme inhibitor (ACEI) or angiotensin receptor blocker (ARB), β-blockers, aldosterone receptor antagonist, digitalis and vasodilating agents could be used as the regular medication in participants. The hospitalization period is 2 ± 1 weeks.

### Trial treatment

The program for Group A is as follows (Fig. 1):

**Figure 1 F1:**
[figure not shown]
**The General Process of SECE-TCM**.

Based on the regular medication, the medicines like polarized solution (500 ml, Qd), which are considered as neutral treatment and the same fluid volume to Group B, can be used intravenously during the hospitalization period. After discharging, two kinds of placebo drugs, which are visually identical to Group B, should be selected and prescribed for 6 months according to the differentiation of *qi-yang *or *qi-yin *syndrome (Table 1). For the patients who suffer from *qi*-*yang *deficiency (combined with blood stasis and/or phlegm retention), the placebo drug of *Qiliqiangxin *Capsule should be taken. Conversely, the placebo drug of *Buyiqiangxin *tablets can be applied in those with *qi*-*yin *deficiency (combined with blood stasis and/or phlegm retention). Only one kind of them will be taken 4 pieces each time and 3 times a day.

**Table 1 T1:** The Standardization of TCM Differentiation.

	*Qi yang *deficiency	*Qi yin *deficiency
**Main symptoms**	**Palpitation, shortness of breath, tired and fatigue**	

Secondary symptoms	Spontaneous perspiration, aversion to cold and cold limbs, anorexia and abdominal distension, loose stool, soreness and lumbago, dizziness and amnesia, pale complexion, dark pale tongue or pale and corpulent tongue with teeth prints, deep slow or irregularly intermittent pulse.	Spontaneous/night perspiration, dizziness and restlessness, dry mouth, dark red zygoma, red tongue with little coating, thready and rapid pulse or irregularly intermittent pulse.
Combined syndromes	1. Blood stasis: Dull pain on the chest, cyanotic lips, raised jugular venous pressure, dark or purple tongue with petechia, and hesitant pulse.	
	2. Phlegm retention: Swelling face and limbs or other parts of body, oliguria, chest fullness, cough with sputum, white and slippery tongue coating	

P.S. If the patient has the main symptom, two or more secondary symptoms with the proper tongue and pulse characters, and either one or two item of the combined symptoms, he/she can be diagnosed as heart failure disease with certain TCM syndrome.

The program for Group B is as follows (Fig. 1):

Based on the regular medication mentioned above, during the hospitalization period, the patients who are *qi*-*yang *deficient can take *Shenfu *Injection (60 ml) with 5%glucose (250 ml) intravenously guttae once daily. For those who are *qi-yin *deficient, *Shenmai *Injection (60 ml) with 5%glucose (250 ml) can be applied intravenously guttae once daily. For both, *Danhong *Injection (40 ml) will be used with 5%glucose or physiological saline (250 ml) intravenously guttae once daily. After discharging, different drugs should be selected for 6 months according to the differentiation of *qi-yang *or *qi-yin*. For the patients who suffer from *qi*-*yang *deficiency (combined with blood stasis and/or phlegm retention), *Qiliqiangxin *Capsule should be taken. Conversely, *Buyiqiangxin *tablets can be applied in those with *qi*-*yin *deficiency (combined with blood stasis and/or phlegm retention). Only one of them will be taken 4 pieces each time and 3 times a day.

*Shenfu *injection (Batch number: 081202), *Shenmai *injection (Batch number: 081125) and *Danhong *Injection (Batch number: 090410) which are used in the hospitalized period are made in *Yaan Sanjiu *Medical and Pharmaceutical CO. LTD, *Chiatai Qingchunbao *Pharmaceutical CO. LTD and *Buchang *Group separately. The *Qiliqiangxin *Capsule (Batch number: 080601), *Buyiqingxin *Tablets (Batch number: 080701) their models (Batch number: 080701 and M090101 separately) are supported by *Hebei Yiling *Pharmaceutical CO. LTD and *Suzhou Zilu *Pharmaceutical CO. LTD freely.

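### Group A's 500 mL daily infusion is declared equal in fluid volume to Group B's, but the stated Group B volumes add to 600 mL a day

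*Protocol article*

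**What the plan says.** All the volumes stand under Trial treatment in the protocol article.

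- **Group A, in hospital.** On top of regular medication, patients may receive "the medicines like polarized solution (500 ml, Qd"), in a class of infusions "which are considered as neutral treatment and the same fluid volume to Group B, can be used intravenously during the hospitalization period".
- **Group B, in hospital, first infusion.** Qi-yang patients are assigned Shenfu and qi-yin patients Shenmai. The volumes are the same for both. For qi-yang the text gives "Injection (60 ml) with 5%glucose (250 ml) intravenously guttae once daily", and for qi-yin "Injection (60 ml) with 5%glucose (250 ml) can be applied intravenously guttae once daily".
- **Group B, in hospital, second infusion.** All patients, whatever the syndrome, have Danhong: "Injection (40 ml) will be used with 5%glucose or physiological saline (250 ml) intravenously guttae once daily".

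The Western medication section sets the hospital stay at 2 ± 1 weeks. Data collection instruments lists discharge as an assessment point, with NYHA class, the six-minute walking test and BNP among the items measured. The primary outcome is cardiovascular death, and Follow-up sets a 12-month observing period.

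**The concern.** The article makes a specific claim about its control, namely equal fluid volume, and then prints component volumes that do not bear it out. This is a disagreement between stated figures, not a detail lost in condensing a longer protocol, and an analysis plan would not settle it.

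The claim has a purpose. After discharge, Group A takes placebos that look the same as the Group B products. In hospital, the infusion is the only control feature that the article describes. The designers chose fluid volume as something to equalise in patients with heart failure. If it is not equal, a reader of the discharge results would be told that fluid had been balanced when, on the stated figures, it had not.

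**Working it through.** **Inputs** (mL per day, from Trial treatment; stay from Western medication)

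- Group A infusion: 500, once daily
- Group B first infusion: 60 injection + 250 diluent, once daily, in either syndrome
- Group B second infusion: 40 injection + 250 diluent, once daily, all patients
- Stay: 2 ± 1 weeks, that is 7 to 21 days

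**Can the declared equality be reproduced?** It requires Group B = 500.

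- Total volume: (60 + 250) + (40 + 250) = 310 + 290 = 600. Not equal to 500.
- Diluent only: 250 + 250 = 500. Equal.
- Each 250 mL read as the final made-up volume: 250 + 250 = 500. Equal, but the text gives the injection *with* 250 mL, not made up to 250 mL.

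On the plain reading, the equality fails.

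**Size of the gap**

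- Per day: 600 − 500 = 100 mL, which is 100/500 = 20% of Group A's volume, or 100/600 = 16.7% of Group B's
- Over 7 days: 100 × 7 = 700 mL
- Over 14 days: 100 × 14 = 1,400 mL
- Over 21 days: 100 × 21 = 2,100 mL

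**Is the infusion optional in one arm only?** The relevant verbs, side by side:

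- Group A: "can be used intravenously during the hospitalization period"
- Group B, Shenfu: "deficient can take"
- Group B, Shenmai: also *can*, in the sentence on that injection
- Group B, Danhong: *will*

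The same permissive verb governs the Group A infusion and the first Group B infusion. If *can* truly meant optional, a Group B patient could receive Danhong alone, 40 + 250 = 290 mL, which is 500 − 290 = 210 mL less than Group A. A literal reading therefore leaves the gap open in either direction.

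**The case against.** The strongest defence is that the diluents match exactly at 500 mL, and that the designers probably meant this. The remaining 100 mL is the two herbal injections, which are the assigned treatment. On that view the control is slightly imperfect and nothing more. The explanation is plausible, and it is why the point is not graded higher. It does not rescue the wording, because the article claims equal fluid volume without limiting the claim to diluent.

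Three stronger readings are tempting, and the document does not support them.

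- *The control infusion is optional while Group B's is compulsory.* A reader might infer this from the verb *can* and reach a gap of 600 mL a day, or 600 × 7 to 600 × 21 = 4.2 to 12.6 L. But Group B's first infusion carries the same verb. For the oral drugs, too, the article uses *should* for one syndrome and *can* for the other, in both arms, with no sign that a different obligation is meant. The verb is loose English. A control patient left without an infusion would also defeat the stated aim of equal volume.
- *The in-hospital comparison is confounded by fluid.* The extra volume comes with the randomised treatment, so this is incomplete matching rather than confounding. Nothing in the document shows that 100 mL a day changes any measurement.
- *The primary result is compromised.* The gap lasts one to three weeks, diuretics are part of the permitted regular medication, and the outcome is cardiovascular death over 12 months. Events in hospital would fall within observation if time runs from enrolment, as the Abstract says, but no effect on them is shown.

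The open description of the control solutions could also be criticised. A list of permitted solutions is something that a condensed article may leave to the full protocol, and Figure 1 could not be consulted, so no finding rests on it.

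**Conclusion.** The point holds as an internal contradiction. On the article's own figures, Group B receives 600 mL a day and Group A 500 mL, so the arms are not matched for total fluid. The gap is 100 mL a day, or 0.7 to 2.1 L over the stay. This assumes that each infusion is given as written on every day of a 7-to-21-day stay, and that injection and diluent volumes add.

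A small contribution of fluid to measurements taken at discharge, such as BNP, NYHA class and the six-minute walk, cannot be excluded. Its size cannot be estimated from the document. An effect on 12-month cardiovascular death is not shown. Confidence is high in the arithmetic and low in any consequence for outcomes. Severity is minor to moderate.

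**What to change.** Reconcile the Group A and Group B programmes under Trial treatment so that the stated volumes and the equality claim agree. If the volumes are as intended, withdraw the claim of equal fluid volume or limit it to diluent, and state that the in-hospital comparison includes this difference. Which fluid and which volume to use is for the clinical team.

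In either case, report daily infused volume by arm beside the discharge outcomes, so that readers can see what each arm received.

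The cost is a change of wording and, if it is not already collected, one field on the case report form. No extra patients are needed, and the primary analysis does not change.

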### Follow-up

The observing period is 12 months, which includes a 6-month experimental medication period and a 6-month follow-up period. At admission, discharging and each follow-up point (Fig. 2), each patient's general data and their four diagnostic results in TCM should be recorded (Table 2). During the observing period, other herbs with noted cardiac effects are forbidden for prescription or personal use. The patients should be followed-up for 12 months, except the dead ones.

**Table 2 T2:** Definitions used in SECETCM-HF.

Term	Definition
Differentiation	By TCM diagnostic method, to differentiate patients' TCM syndrome comprehensively, and then determine the treating principles based on it.
*Qi *Deficiency	Insufficiency of vital *Qi *or dysfunction of *Qi*
*Yin *Deficiency	Insufficiency of essence, blood or body fluid
*Yang *Deficiency	Insufficiency or dysfunction of *yang Qi*
Blood Stasis	Unsmooth blood circulation
Phlegm Retention	Concrete or invisible pathological products caused by dysfunction of body fluid metabolism
Cardiac Ultrasound Indexes	Using improved-Simpson method to calculate ESV, EDV and EF, et al.
The information obtained by TCM four diagnostic methods	The items of TCM syndromes, tongue and pulse characters by inspecting, listening to the sound and smelling the odors, inquiring and pulse-taking.
Quality of Life	Evaluating the quality of life by Minnesota Quality of Life scale combined with TCM characteristic items

**Figure 2 F2:**
[figure not shown]
**The Implementation of SECE-TCM**.

### Primary outcome measurement

The primary outcome measure is "cardiovascular death incidence".

### Secondary outcome measurement

The following secondary outcome measures will be assessed:

• HF re-admission.

• Other cardiovascular events: including acute coronary syndrome, serious cardiac arrhythmias, cardiac shock, stroke, pulmonary embolism and peripheral vascular incidences.

• Non-cardiovascular events: including upper gastrointestinal hemorrhage, kidney failure and tumor.

### Measures of health-related quality of life

The Modified Minnesota Quality of Life Scale consists of the items of its own and the additional items with TCM characteristics. It's one of the special features in the study, and used as an evaluation principle for HF fulfilled with Chinese culture elements.

### Measures of safety

From admission to the 3^rd ^and 6^th ^month interval during the follow-up period, regular examinations should be provided. The vital signs of the patients, such as the heart rate and blood pressure, should be recorded before and after treatment. Blood and urine routine examination, hepatic and renal function, as well as electrolytes in blood should also be tested. Moreover, ECG should be recorded at each follow-up period. The adverse events, especially the severe ones, should be reported to the leader of the hospital and drug administration.

### Data collection

Clinical research format should be completed at each follow-up point by the investigators. All patients enrolled will be recorded.

The statisticians from the statistics center in Tianjin University of Traditional Chinese Medicine and the mathematics experts from Nankai University are responsible for the statistic process and data mining.

### Data collection instruments

The patients should be evaluated at the points of admission, discharging, and the 1^st^, 3^rd^, 6^th^, 9^th^, 12^th ^month after leaving hospital (Fig. 2). The items below should be measured:

• NYHA classification.

• Lee's heart failure score

• Six-minute walking test (6MWT)

• The scoring of the four diagnosis of TCM

• Quality of life scale

• The withdrawal and decreasing of HF drugs.

• General examination in clinic, including cardiac ultrasound, chest radiography, ECG, the plasma level of angiotensin and aldosterone, blood and urine routine examination, hepatic and renal function, as well as electrolytes in blood.

• Inflammatory cytokines (TNF-α, IL-1, IL-6) and BNP

### Sample size

The fatality rate of patients with HF in China is about 24.24% [10] when they are prescribed medication including diuretics, ACEI or ARB, β-blockers and vasodilating agent. In a retrospective study of the First Teaching Hospital of Tianjin University of TCM, the rate was below 10%. The power calculation is based on the fatality rates at the 5% significance level. There should be 140 patients in each group. Concerning the loss to follow-up rate, the study needs 340 patients in all.

### Method of randomization

The central randomization system makes the study possible. The trial center gives the unique enrollment number of each participant, then records and preserves the information after randomization. Each hospital could assign only 1 to 2 investigators as contact person to send the patients' information to the central randomization system, and get feedback on the patient's random group.

### Statistical analyses

For the statistical analysis, both medical statistic method and complex mathematical methods will be used. The case-distribution, commeasurable analysis, patients' compliance, therapeutic effect analysis, security analysis and correlation analysis are determined by the statistical method. Focusing on the occurrence and corresponding time of the cardiovascular events, product-limit method, Log-Rank test and Kaplan-Meier curve will be applied. Meanwhile, the total risk rate will be analyzed by the Cox proportional hazard regression. The complex mathematical methods include the rough set, random graph and support vector machine.

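### One minus Kaplan-Meier, if read as incidence, overstates HF re-admission and other non-fatal cardiovascular events, and by more in the arm with higher mortality

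*Protocol article*

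**What the plan says.** For event times, the Statistical analyses section of the protocol article names one estimator and one test: "Focusing on the occurrence and corresponding time of the cardiovascular events, product-limit method, Log-Rank test and Kaplan-Meier curve will be applied". It adds that "the total risk rate will be analyzed by the Cox proportional hazard regression". It names no cumulative incidence function and no competing-risk method.

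The outcomes to which this applies are set elsewhere in the Methods:

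- The primary outcome is "cardiovascular death incidence", which is the incidence of one cause of death.
- The first secondary outcome is "HF re-admission", listed without death. The next item begins "Other cardiovascular events: including acute coronary syndrome, serious cardiac arrhythmias". The word 'other' implies that re-admission is itself counted as a cardiovascular event.
- A further item, "Non-cardiovascular events: including upper gastrointestinal hemorrhage, kidney failure and tumor", shows that serious non-cardiovascular illness is foreseen, but no frequency is given.
- The Follow-up section sets 12 months of observation for everyone who does not die.
- The Sample size section plans on fatality rates of 24.24% and below 10%.

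**The concern.** A patient who has died cannot later be re-admitted for heart failure, and a patient who dies of cancer cannot later die of a cardiovascular cause. The product-limit method for a single event type removes such patients from the risk set as censored, as if they could still have had the event. One minus Kaplan-Meier then estimates a net risk in a world without the competing deaths. It does not estimate the share of randomized patients who have the event within 12 months.

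This matters more than usual here because the planning figures make mortality both substantial and unequal. If treatment works as planned, the overstatement is larger in the arm with more deaths. A therapy that keeps patients alive leaves more of them exposed to re-admission, and the Kaplan-Meier curves would not show this.

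**Working it through.** **Inputs from the protocol**

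- Fatality rates of 24.24% and below 10% (Sample size); 10% is used for the second.
- 12 months of follow-up, ended early by death (Follow-up).
- 140 patients per group, 340 in all (Sample size).

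**Assumptions, because the protocol does not give them**

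- The two fatality rates are 12-month all-cause mortality, with 24.24% in Group A and 10% in Group B.
- Hazards are constant over the year.
- The net 12-month re-admission risk is 20-50% and equal in both arms.
- The non-cardiovascular share of deaths is 10-30%; alternatively, there is an equal 1-5% risk of non-cardiovascular death in each arm.

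**Is it fair to read the two rates as the arms' rates?** The protocol gives no incidence figure that would test this point, but its sample size supports the reading. Power is not stated. With 90% power and two-sided 5% assumed, the unpooled formula gives

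n = (1.960 + 1.282)² × (0.2424 × 0.7576 + 0.10 × 0.90) / 0.1424² ≈ 142 per group,

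close to the stated 140. This makes the reading plausible without proving it. The sample size has no other bearing on the point.

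**Formulas.** With event hazard λ₁ and competing-death hazard λ₂ over one year:

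- One minus Kaplan-Meier = 1 − exp(−λ₁)
- Cumulative incidence (CIF) = λ₁/(λ₁ + λ₂) × [1 − exp(−(λ₁ + λ₂))]

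**HF re-admission, any death competing.** λ₂ = −ln(0.7576) = 0.2776 in Group A and −ln(0.90) = 0.1054 in Group B. For a net risk of 30%, λ₁ = −ln(0.70) = 0.3567.

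- Group A: 0.3567/0.6343 × (1 − 0.70 × 0.7576) = 0.5623 × 0.4697 = 26.4%
- Group B: 0.3567/0.4620 × (1 − 0.70 × 0.90) = 0.7720 × 0.37 = 28.6%
- Kaplan-Meier: 30.0% in both

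Over the assumed range (percent and percentage points, differences taken before rounding):

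| Kaplan-Meier, both arms | CIF A | Excess A | CIF B | Excess B | Hidden difference, B − A |
|---|---|---|---|---|---|
| 20 | 17.55 | 2.45 | 19.02 | 0.98 | 1.47 |
| 30 | 26.41 | 3.59 | 28.56 | 1.44 | 2.15 |
| 40 | 35.34 | 4.66 | 38.13 | 1.87 | 2.80 |
| 50 | 44.36 | 5.64 | 47.74 | 2.26 | 3.39 |

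The direction is the same in every row. The excess shrinks as the event becomes rarer, so other non-fatal events with risks below 20% would be affected less.

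**Cardiovascular death, non-cardiovascular death competing.** If a share s of the planned deaths D is non-cardiovascular, CIF = (1 − s)D and one minus Kaplan-Meier = 1 − (1 − D)^(1 − s).

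| s | A: Kaplan-Meier / CIF | Excess A | B: Kaplan-Meier / CIF | Excess B |
|---|---|---|---|---|
| 10% | 22.11 / 21.82 | 0.29 | 9.05 / 9.00 | 0.05 |
| 20% | 19.91 / 19.39 | 0.52 | 8.08 / 8.00 | 0.08 |
| 30% | 17.66 / 16.97 | 0.69 | 7.11 / 7.00 | 0.11 |

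If instead 24.24% and 10% are net cardiovascular risks and non-cardiovascular risk is an equal 1-5%, the excess is 0.12-0.58 points in A and 0.05-0.25 points in B. With no non-cardiovascular deaths it is zero.

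**Scale against sampling error.** At 40% net risk the standard error of the difference in crude incidence is √[(0.3534 × 0.6466 + 0.3813 × 0.6187)/n]. That is 5.8 points at n = 140 per arm and 5.2 points at n = 170. The hidden 2.8 points is about half a standard error.

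**The case against.** The strongest reply is that a condensed article is being held to detail it does not contain. The analysis sentence speaks only of cardiovascular events. It does not list endpoints, state a censoring rule, or say that one minus Kaplan-Meier will be reported as 12-month incidence, and it could cover a composite that includes death. An analysis plan that is not shown may add competing-risk methods. This stands in part: the point applies to the curves when they are read as incidence for events that death can prevent. It does not remove the point. The article positively names the product-limit method for these events, and a plan that follows it would carry the problem forward.

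A second reply is that equal Kaplan-Meier curves in the example are correct in their own terms, since the cause-specific re-admission hazards were set equal. That is right. The curves mislead only when crude incidence is the target, and the protocol uses the word incidence for cardiovascular death but not for re-admission. This supports reporting both quantities clearly labelled, and does not justify leaving out the crude one.

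A third reply concerns size, and it largely stands. The re-admission figures rest on assumed risks, the Sample size section gives no time horizon for 24.24% and does not expressly assign the rates to arms, and the hidden difference is within sampling error.

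A reader might infer that the primary analysis is biased or its test invalid. The documents do not support this. The log-rank test and Cox model are valid for the cause-specific hazard, and the effect on the primary outcome is under 1 point against a crude difference of about 10-13 points in the scenarios for s above.

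**Conclusion.** The point holds as one of estimation and labelling, chiefly for HF re-admission and other non-fatal cardiovascular events. Read as incidence, one minus Kaplan-Meier is too high. Under the stated assumptions the excess for re-admission is about 2.5-5.6 points at 24.24% mortality and 1.0-2.3 points at 10%, which can hide a crude difference of about 1.5-3.4 points. The direction follows from the estimator. The size depends on the assumed re-admission risk, on equal re-admission hazards, and on treating the planning fatality rates as 12-month mortality by arm. For cardiovascular death the excess is below 1 point and depends on non-cardiovascular deaths occurring at all. The change is worth making because it is simple and the distortion is foreseeable, but the primary comparison does not depend on it.

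**What to change.** In the Statistical analyses section or the analysis plan, specify:

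- Aalen-Johansen cumulative incidence for HF re-admission and other non-fatal cardiovascular events, with death from any cause as the competing event.
- Aalen-Johansen cumulative incidence for cardiovascular death, with non-cardiovascular death as the competing event.
- Log-rank and Cox results kept as planned and labelled as cause-specific.
- Kaplan-Meier kept for all-cause death, where no competing event arises.

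A new composite of cardiovascular death and re-admission is not needed for this correction. The cost is a few lines of analysis text and standard software. The only data needed are the date and cause of death, which the primary outcome already requires, and the event dates, which the planned time-to-event analysis already requires.

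### The only hypothesis test named for cardiovascular events uses no baseline information; a Cox model adjusted for a few admission values would be more efficient if those values are prognostic

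*Protocol article*

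**What the plan says.** The primary outcome is the incidence of cardiovascular death (Protocol article, Primary outcome measurement). For the occurrence and timing of cardiovascular events, the Statistical analyses section states: "product-limit method, Log-Rank test and Kaplan-Meier curve will be applied". No stratification factor or covariate is attached. The next sentence adds: "the total risk rate will be analyzed by the Cox proportional hazard regression". That risk rate is not defined, the model's covariates are not listed, and the section does not say which method decides the primary comparison.

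On baseline data, the Data collection instruments section says: "The patients should be evaluated at the points of admission, discharging", followed by visits up to month 12. The items include NYHA class, Lee's heart failure score, the six-minute walk, cardiac ultrasound (Table 2 shows that this yields EF) and BNP.

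The Sample size section works from crude rates: "The power calculation is based on the fatality rates at the 5% significance level". The rates are 24.24% from a cited source and below 10% from a retrospective series. It concludes: "There should be 140 patients in each group".

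**The concern.** A log-rank test without strata compares the groups as if all patients had the same prognosis. Here they probably do not: eligibility admits NYHA II to IV, any LVEF up to 50%, ages 40 to 79, and BNP from 200 pg/mL with no upper limit. If admission values predict cardiovascular death, a test that uses them has more power from the same patients and corrects for chance imbalance in severity.

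The number of events is modest, at about 48 on the planning rates, so a more efficient test is worth having. The data it needs are already being collected.

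**Working it through.** **Inputs from the document.** Group A rate 24.24%; comparison rate below 10%; 5% significance; 140 per group; 12 months.

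**Assumptions.** 10% is the Group B rate; the test is two-sided; power is 85-90% (none is stated); the prognostic strength of the admission values is unknown and is varied.

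**1. The plan's own figure.** Two proportions, unpooled variance, 90% power:

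n = (1.960 + 1.282)² × (0.2424 × 0.7576 + 0.10 × 0.90) / (0.2424 − 0.10)² = 10.51 × 0.2736 / 0.02028 ≈ 142 per group.

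With continuity correction at 85% power the result is 138. So 140 is consistent with these rates at about 85-90% power. Power at n = 140 is 89.0%.

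**2. Events.** 140 × 0.2424 + 140 × 0.10 = 33.9 + 14.0 ≈ 48. The number is lower if the Group B rate is below 10%, or if only cardiovascular deaths count, since the planning rates are described as fatality.

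**3. Unadjusted power on the hazard scale.** HR = ln(0.90)/ln(0.7576) ≈ 0.38. Schoenfeld: Φ(√47.9/2 × |ln 0.38| − 1.96) ≈ 91.8%.

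**4. Gain from adjustment.** Trials were simulated with 140 per group, 12 months of follow-up and the 12-month group rates held fixed, 2,500 runs per scenario. An unadjusted Cox Wald test stood in for the log-rank test and was compared with a Cox model that includes the baseline score. Gain = (mean adjusted z / mean unadjusted z)² − 1. A Group B rate of 12.12% (half the control rate) was added as a less favourable case; it is not in the document.

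| HR per SD of score (assumed) | Gain, 24.24% v 10% | Power, unadjusted → adjusted | Gain, 24.24% v 12.12% | Power, unadjusted → adjusted |
|---|---|---|---|---|
| 1.0 | 0% | 0.897 → 0.899 | 0% | 0.761 → 0.759 |
| 1.5 | 3% | 0.903 → 0.908 | 3% | 0.748 → 0.760 |
| 1.8 | 7% | 0.900 → 0.916 | 7% | 0.743 → 0.776 |
| 2.2 | 13% | 0.887 → 0.926 | 15% | 0.742 → 0.813 |
| 2.7 | 23% | 0.896 → 0.946 | 25% | 0.757 → 0.844 |
| 3.3 | 35% | 0.887 → 0.957 | 38% | 0.756 → 0.874 |

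On 280 patients, 3% is about 8 patients, 13-23% is about 36-64, and 35-38% is about 98-106.

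**5. Cross-checks.** A separate simulation with four independent normal covariates and a total log-hazard SD of 0.8-1.0 (HR per SD 2.2-2.7) gave 12-20%, with type I error of 0.049-0.052. By the approximation 1/(1 − R²) − 1, a gain of 12-20% needs R² of about 0.107-0.167.

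**6. Room for covariates.** Four covariates plus treatment make five parameters: 48/5 ≈ 9.6 events per parameter. Entering NYHA II-IV as categories makes six, and 48/6 = 8.

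**The case against.** The strongest reply is that nothing here is wrong. Kaplan-Meier curves, a log-rank test and a Cox model form a valid set, randomisation protects the type I error, and an unadjusted comparison matches a trial sized on crude rates. A condensed article may also leave the covariate list and the choice of primary method to the full protocol or analysis plan. This stands as far as it goes: an unlisted covariate is no fault in this article. What remains is that the article does name a test for cardiovascular events, and that test makes no use of admission data. The Cox model beside it is attached to an undefined quantity.

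A reader might infer that the trial is committed to an unadjusted log-rank test and so forfeits some 12-20% of its sample size. The document supports neither part. It plans a Cox regression in the next sentence, which could carry covariates, and ranks neither method first. The 12-20% follows only from an assumed prognostic strength.

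The simulations are also favourable to adjustment, because the covariates are complete and correctly modelled. In practice BNP below 200 pg/mL is excluded, LVEF is capped at 50% and NYHA has three levels. This may narrow the spread and lower the gain.

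**Conclusion.** This is an efficiency improvement. The named log-rank test is valid, and the planned comparison is not shown to be underpowered: at 24.24% versus 10% its power is about 89-92%. Adjustment for admission values would add the equivalent of about 3% to 35-38% more patients for hazard ratios of 1.5 to 3.3 per SD of the combined score, about 13-23% at 2.2-2.7, and nothing if the values carry no prognostic information. Those strengths are assumptions. The result also takes 10% as the Group B rate and fatality as a stand-in for cardiovascular death. In absolute terms the power gain is a few points at the planning rates, and larger if the true effect is smaller.

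**What to change.** State in the Statistical analyses section, before outcomes are examined by group, that the primary test of cardiovascular death is the treatment term of a Cox model adjusted for a short fixed list of admission values. One workable list is log BNP, NYHA class as a single ordered term, LVEF and age. Keep it to about four terms, given about 48 expected events and possibly fewer. Retain the Kaplan-Meier curves and the log-rank test as supportive.

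The cost is one sentence and no new data. There are two small downsides. First, the hazard ratio becomes conditional on the covariates and lies somewhat further from 1: with the 12-month rates held at 24.24% and 10%, it was 0.355 at an HR per SD of 2.2 and 0.339 at 2.7, against 0.38 with no prognostic score. Second, a simple rule for missing admission values must be written down.
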